#### Secondary outcomes (table 1)

VAS for back pain;VAS for leg pain; andODI.

The data will be collected preoperatively; on day 1 postoperatively; and then at 3, 6, 12 and 24 months postoperatively.

### Statistical analysis

All data will be analysed using SPSS V.19.0 software. The differences in wound incision length, operative time, intraoperative blood loss and angles between the two groups will be analysed using a two independent-sample t-test with an α of 0.05. VAS and ODI scores at preoperation, postoperation, 3 months postoperatively, 6 months postoperatively and 12 months postoperatively will be analysed using a repeated-measures analysis of variance. The times of X-ray exposure and frequency of screw penetration out of the cortex will be compared using the χ^2^ test.

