**Figure 5 F5:**
[figure not shown]
One example of the experiment on conducted 3D printed lumbar model before clinical application to make sure the accurate screw trajectory.

The 3D navigation template will be sterilised and used to guide the screw in further operations on the patients. In experimental group, the dissection of the paraspinal tissue will performed at one side to expose the part of spinous process, laminar and facet joint; the 3D navigation template will be attached to the surface of the above bony construction. Then, the Kirschner wire (K-wire) will be inserted inside the 3D navigation template, and a trajectory for the screw will be fashioned with a cannulated drill; screws will be subsequently introduced. In the control group, multiple X-ray fluoroscopy will be used, and the screw trajectory will be adjusted by intraoperative X-ray fluoroscopy.

After the operation, CT scans of the patients in both groups will be obtained, and the α1, β1, γ1, δ1 and ε1 angles will be measured corresponding to the angles of the optimal screw trajectory in 3D images. The placement and position of the screws will be divided into three types (type I, the screw does not penetrate out of the cortex; type II, the screw partially penetrates out of the cortex, but by less than 2 mm; and type III, the screw penetrates out of the cortex by more than 2 mm).

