### Outcome measure

#### Primary outcomes (table 1)

**Table 1 T1:** The data need to collect through the research

	Baseline	Perioperation	Postoperation				
Assessment	−1 day	Day 0	Day 1	3 months	6 months	12 months	24 months
Eligibility criteria	×						
Recruitment	×						
Informed consent	×						
Randomisation	×						
Baseline demographics	×						
Medical history	×						
X-ray exposure		×					
Wound incision length		×					
Operative time		×					
Blood loss		×					
Complications		×	×	×	×	×	×
Screw angles							
α1			×				
β1			×				
γ1			×				
δ1			×				
ε1			×				
The position of the screws			×				
VAS of back pain	×		×	×	×	×	×
VAS of leg pain	×		×	×	×	×	×
ODI	×		×	×	×	×	×

ODI, Oswestry Disability Index; VAS, visual analogue scale.

Screw angles compared with the optimal screw trajectories in the 3D digital images and the position of the screws.Wound incision length, operative time, intraoperative blood loss, times of X-ray exposure and complications.

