## Discussion

Translaminar facet screw fixation has been reported as a minimally invasive technique,^11 12 23^ and biomechanical comparisons between facet screw and pedicle screw fixation have revealed biomechanical equivalence between them.^14 15 24^ Unilateral lumbar pedicle screw may be used by some surgeons; however, Sethi *et al*^25^ used in vitro human cadaveric lumbar spines to compare the biomechanical properties of bilateral pedicle screws, unilateral pedicle screws (UPSs), UPSs and translaminar facet screws, and unilateral single pedicle screws and translaminar facet screws (V construct). They found that the UPS construct was the least stable in all loading modes and that the added translaminar facet screw enhanced the stability and stiffness. Similar results were obtained from a finite element analysis study.^26^ The biomechanical study of Luo *et al*^27^ revealed that a significantly larger displacement of the contralateral articular process was recorded in a model with only unilateral pedicle screws, and they reported that the unilateral pedicle screw combined with a contralateral translaminar facet screw had an instant and long-term equivalent biomechanical ability to that of the traditional bilateral pedicle screw (making it an alternative to the bilateral pedicle screw) and could be less invasive while maintaining stable and effective instrumentation.

Current computer-assisted surgery systems can achieve the accurate screw trajectory; however, the cost of computer-assisted surgery systems is considerable, and the manipulation is too complicated,^28^ whereas the accuracy remains dependent on multiple radiations.

Combining 3D reconstruction and 3D rapid printing is a new mode of production, which is applied in many fields because of the advantages of visualisation, plasticity and rapid printing.^29–31^ Moreover, 3D printing templates can help surgeons to achieve accurate screw placement for posterior cervical fixation and scoliosis.^32 33^

In this study, we will compare the 3D navigation template to multiple X-ray fluoroscopy for guiding a unilateral lumbar pedicle screw with contralateral translaminar facet screw fixation. The compared results will include the perioperative parameters (such as X-ray exposure, wound incision length, operative time, blood loss); screw angles of α1, β1, γ1, δ1 and ε1; postoperative complications; the VAS of back and leg pain; and the ODI.

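### The analysis section t-tests screw angles without defining them as absolute deviation from each patient's plan, so the five angle comparisons, taken as written, do not measure the stated accuracy outcome

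*Protocol article*

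**What the plan says.** Under Primary outcomes, the protocol article lists "Screw angles compared with the optimal screw trajectories in the 3D digital images and the position of the screws". The Study procedure section describes three planned angles for the translaminar facet screw (α, β, γ) and two for the pedicle screws (δ, ε), taken from an individual preoperative design. After surgery, both groups have CT, and the matching achieved angles α1 to ε1 "will be measured corresponding to the angles of the optimal screw trajectory in 3D images". The outcome is therefore closeness to a patient-specific plan, and the quantities needed to compute it are described.

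The Statistical analysis section then says that "intraoperative blood loss and angles between the two groups will be analysed using a two independent-sample t-test". The plan or optimal trajectory does not appear in that sentence. The Discussion lists among the compared results "screw angles of α1, β1, γ1, δ1 and ε1", which are the achieved angles. Table 1 also lists only α1 to ε1.

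Screw position is a separate item within the same primary outcome. For it, "frequency of screw penetration out of the cortex will be compared using the χ^2^ test".

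**The concern.** The outcome asks how close each screw came to its own plan. A two-sample t-test on angles asks whether the average angle differs between the groups. Planned angles vary with the patient's anatomy and the operated level, and randomisation makes their averages equal in expectation. Two techniques that both centre on the plan will therefore give the same average achieved angle, even if one scatters far more widely. Signed differences have the same weakness, because errors to either side cancel.

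At stake is the reading of five primary comparisons. A real gain in precision could be reported as no difference. A significant difference in mean angle would not say which technique was closer to plan. Leaving the choice among raw, signed and absolute angles until the data are in would also allow the result to guide the choice.

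**Working it through.** **Structure.** Write the achieved angle as A = P + e, where P is the patient's planned angle and e is the placement error, with mean b and SD s in each arm (T template, C control). Randomisation makes the mean of P equal in expectation.

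- Raw angle: expected group difference = b_T − b_C.
- Signed deviation A − P: expected group difference = b_T − b_C.
- Absolute deviation |A − P|, normal errors with b = 0: mean = s·√(2/π) = 0.798·s, so expected difference = 0.798·(s_T − s_C).

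The first two expressions do not contain s. If b_T = b_C, the t-test on raw or signed angles has a true null, and its rejection rate is close to α whatever the two SDs are.

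**Sample size used.** The protocol's 132 comes from 84.6% versus 95%, power 0.8, α 0.05. With pooled variance, two-sided and without continuity correction:

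n = [1.960·√(2·0.898·0.102) + 0.842·√(0.846·0.154 + 0.95·0.05)]² / 0.104² = (0.839 + 0.355)² / 0.010816 ≈ 132 per group.

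The text does not say whether 132 is per group or in total, so both 132 and 66 per arm are shown below. This calculation concerns proportions and is not affected by the present point.

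**Assumptions.** The protocol gives no angle SDs. Assumed: planned-angle SD 3, 6 or 10 degrees; template error SD 2 degrees; control error SD 2, 3, 4 or 6 degrees; control offset 0, or 2 degrees in one setting; normal errors. There were 4,000 simulated trials per setting, with a t-test at 0.05. Ranges are over the three planned-angle SDs.

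| Error SD T vs C; control offset | n per arm | Raw angle | Signed deviation | Absolute deviation |
|---|---|---|---|---|
| 2 vs 2; 0 | 66 or 132 | about 5% | about 5% | about 5% |
| 2 vs 3; 0 | 66 | about 5% | about 5% | 85–86% |
| 2 vs 3; 0 | 132 | about 5% | about 5% | 99% |
| 2 vs 4; 0 | 66 or 132 | about 5% | about 5% | over 99% |
| 2 vs 6; 0 | 66 or 132 | about 5% | about 5% | 100% |
| 2 vs 4; 2 | 66 | 19–75% | 95% | 100% |
| 2 vs 4; 2 | 132 | 34–96% | 99.9% | 100% |

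**Hand check of one cell** (2 vs 3, 66 per arm, absolute). The difference is 0.798·(3 − 2) = 0.798. The SD of |e| is s·√(1 − 2/π) = 0.603·s, that is 1.206 and 1.808. SE = √((1.206² + 1.808²)/66) = 0.267. The ratio is 0.798/0.267 = 2.98, and power ≈ Φ(2.98 − 1.96) = Φ(1.02) ≈ 0.85, which agrees with the simulation.

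**With an offset.** In the last two rows the raw-angle test does reject, but it is detecting b_T − b_C. The same difference would arise if the template arm carried the offset. Equal and opposite offsets would also produce a difference, although both arms would then be equally far from plan.

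**The case against.** The best reply is that *angles* in the analysis section is shorthand for the outcome already defined, in a sentence that lists outcomes by short name. The Study procedure section pairs each achieved angle with a planned one, which would serve little purpose if only raw angles were compared. Table 1 is a collection schedule, and planned angles come from the design step, so their absence there proves little. The Discussion sentence is a summary. This reading is coherent, and a reader should not infer that the protocol definitely commits to comparing mean achieved angles. What it does not do is settle the variable. The shorthand could mean signed or absolute deviation, and the signed form has the same weakness when errors centre on the plan. Nor is this only detail left to a fuller document: the article names a test and a variable, and together they do not match its own outcome.

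A second reply is that screw position is a co-listed primary measure of accuracy with its own χ² test. That stands in full. It would be wrong to infer that the trial cannot show an accuracy difference at all.

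A third is that systematic error is also inaccuracy. That stands too. A consistent offset from plan matters, and a signed-deviation test can detect a difference in offset, as the last two rows of the table show. It is not true that only scatter counts.

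A fourth is that the SDs are assumed. The power for absolute deviation depends on them. The rejection rate of about 5% for raw and signed angles does not; it depends on errors centring on the plan in both arms.

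**Conclusion.** The concern holds for the five angle outcomes. The stated analysis does not match the stated outcome, and no section defines a deviation from plan as the variable to be tested. Read literally or as signed differences, the comparison rejects in about 5% of trials when errors centre on the plan in both arms, whatever the difference in precision. With a 2-degree offset in the control arm, the raw-angle test rejects in 19% to 96% of trials, depending on planned-angle SD and sample size, without showing which arm is nearer its plan. Absolute deviation, under the assumed unbiased errors, has power from about 85% (2 vs 3 degrees, 66 per arm) to over 99% (2 vs 4 degrees at either size; 99% for 2 vs 3 degrees with 132 per arm).

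The conclusion about raw and signed angles rests on the structure of the test and on unbiased errors. The power figures rest on assumed normal errors and SDs. The cortical penetration comparison is untouched, and the sample size of 132 is not called into question by this point.

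**What to change.** In the Statistical analysis section, define each angle outcome as the absolute deviation from plan: |α1 − α|, |β1 − β|, |γ1 − γ|, |δ1 − δ| and |ε1 − ε|. State that the plan is set before surgery in the same way in both arms. Compare the groups with a Welch t-test or a rank-sum test, because absolute errors are skewed and their spread is likely to differ between arms. Report the signed deviation as well, as a measure of systematic error. Add the planned angles α to ε to table 1, so that they are visibly recorded for control patients too.

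The cost is a few sentences and one set of rows in the table. The protocol already describes measuring planned and achieved angles; the one thing to confirm is that planned angles are recorded before surgery for every control patient. The definition should be fixed before outcome data are examined.

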#### Sample size calculation

We performed a power analysis to assess the required sample size to show safety with a power (1−b) of 0.8 and α of 0.05. Based on the pre-experiment and related literature,^21^ the proportion of the control group was set to 84.6%, and the proportion of intervention group was set to 95%. We performed a two independent proportions power analysis on PASS (Power Analysis and Sample Size), and the result was 132.

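### Several co-equal primary outcomes are tested without adjustment and none is ranked first, so the single α of 0.05 does not hold for the primary set

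*Protocol article*

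**What the plan says.** All references are to the protocol article.

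- **Primary outcomes (table 1)** has two lines of equal standing: "Screw angles compared with the optimal screw trajectories in the 3D digital images and the position of the screws", and "Wound incision length, operative time, intraoperative blood loss, times of X-ray exposure and complications". That is seven items.
- **Study procedure** shows that the angles are five separate variables: "the α1, β1, γ1, δ1 and ε1 angles will be measured corresponding to the angles of the optimal screw trajectory in 3D images". Table 1 also lists them one by one. The primary set is therefore 5 + 1 + 5 = 11 variables.
- **Abstract, Methods and analysis** also gives a primary list: angles, incision length, operative time, blood loss and complications. Screw position and X-ray exposure are not on it.
- **Statistical analysis** assigns t-tests to incision length, operative time, blood loss and the angles, with 0.05 written for that sentence: "angles between the two groups will be analysed using a two independent-sample t-test with an α of 0.05". It then says "The times of X-ray exposure and frequency of screw penetration out of the cortex will be compared using the" χ² test, with no level given. Complications has no named test.
- **Sample size calculation** is a single two-proportion calculation "to show safety with a power (1−b) of 0.8 and α of 0.05", with 84.6% in the control group and 95% in the intervention group. It does not say which outcome the proportion describes.

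The article does not put any primary outcome ahead of the others, and it states no adjustment of α.

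**The concern.** The sample size section states one α of 0.05 for the trial. The analysis section applies 0.05 to each t-test separately, and the outcomes section makes all the results equally primary. When any of several co-equal primaries can be reported as the primary result, the error rate of the set is not the error rate of one test. A template with no effect on anything would still have a sizeable chance of producing at least one significant primary result.

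The two differing primary lists add to this. A later author could choose between them once the results are known, and two of the seven items are primary in one place and not in the other.

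At stake is what a statement that the trial met its primary outcome would mean. The choice of primary outcomes and the 0.05 level are both written in this article, so the point concerns what the protocol fixes and not detail left to an analysis plan.

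**Working it through.** **1. Reproduce the plan's own figure.** Inputs from Sample size calculation: p₁ = 0.846, p₂ = 0.95, α = 0.05, power 0.8. Sidedness and allocation are not stated; two-sided and 1:1 are assumed.

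n per arm = [z(0.975)·√(2p̄(1−p̄)) + z(0.80)·√(p₁(1−p₁) + p₂(1−p₂))]² / (p₂−p₁)², with p̄ = 0.898.

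- √(2 × 0.898 × 0.102) = 0.4280, times 1.960 = 0.8389
- √(0.1303 + 0.0475) = 0.4216, times 0.8416 = 0.3549
- (0.8389 + 0.3549)² / 0.104² = 1.4251 / 0.010816 = 131.8, rounded up to **132**

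The stated 132 is reproduced as a number per arm, for one test at two-sided 0.05. No variant tried (one-sided, continuity-corrected, unpooled, arcsine) gives 132 as a total.

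**2. Count the tests.**

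| Source | Variables | Number | Level written |
|---|---|---|---|
| t-test | incision, operative time, blood loss, five angles | 8 | 0.05 |
| χ² test | X-ray exposure, cortex penetration | 2 | none (0.05 assumed) |
| no test named | complications | 1 | none (0.05 assumed) |

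The running totals are 8, 10 and 11. On the Abstract's list, the primary outcomes with a named test are the eight t-tests only.

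**3. Chance of at least one significant result in either direction, no true effect, independent tests:** 1 − 0.95^k.

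- k = 8: 33.7%
- k = 10: 40.1%
- k = 11: 43.1%

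**4. Chance of at least one false result favouring the template, independent tests:** 1 − 0.975^k, against a nominal 2.5%.

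- k = 8: 18.3%
- k = 10: 22.4%
- k = 11: 24.3%

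**5. Allow for correlation.** The article gives no correlations, so a common value ρ is assumed for normal test statistics and simulated (400,000 draws, critical value 1.96).

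| ρ | 8 tests, either direction | 8 tests, favouring template | 11 tests, either direction | 11 tests, favouring template |
|---|---|---|---|---|
| 0.3 | 30.0% | 15.2% | 37.5% | 19.0% |
| 0.5 | 25.0% | 12.6% | 30.4% | 15.2% |
| 0.7 | 19.0% | 9.5% | 22.3% | 11.1% |
| 0.9 | 12.0% | 6.0% | 13.2% | 6.6% |

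Every entry exceeds its nominal level (5% or 2.5%).

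**6. Cost of adjusting over all 11.** Holm's first step is 0.05/11 = 0.00455, two-sided critical value 2.838. On the plan's own proportions:

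- Power at 132 per arm = Φ[(√132 × 0.104 − 2.838 × 0.4280)/0.4216] = Φ[(1.195 − 1.215)/0.4216] ≈ **48%**, down from 80%.
- For 80% power at that level: (1.215 + 0.355)² / 0.010816 gives 228 per arm, 456 in total.

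**The case against.** The best defence is that this is a condensed article and an analysis plan may hold a correction or a success rule. That stands for the absence of such a rule taken alone. It does not remove the point, because the article itself sets several co-equal primaries and an unadjusted 0.05. A correction added later would also alter the power that the sample size section states.

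Other limits stand and are reflected in the figures. The 0.05 is written only for the t-tests. Complications has no named test. The 34% to 43% counts results in both directions, so it is not the chance of falsely claiming a benefit; that is the lower set of figures. Positive correlation reduces all of them.

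Three stronger readings are tempting, and the article does not support them.

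- *The X-ray outcome makes a positive trial nearly automatic.* Study procedure says "In the control group, multiple X-ray fluoroscopy will be used", so a difference is to be expected. But a real fall in exposure is a true effect and not a chance finding, and the Introduction gives radiation as a motive for the trial. Nor does the article say that the template arm has no fluoroscopy: segments are identified by C-arm with no distinction between arms.
- *Overall power collapses because all primaries must be significant.* No such rule is stated, and no section gives 80% power to each test.
- *The stated α and power describe none of the planned tests.* If the sized proportion is freedom from cortex penetration, they may well describe that one χ² test. What is lost is error control over the set.

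**Conclusion.** The concern holds in this form: seven co-equal primary items (11 variables), two primary lists that disagree, an unadjusted 0.05 and no outcome ranked first. The single α of 0.05 in the sample size section is therefore not the error rate of the primary set.

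The most secure figure is the one for the eight t-tests, where 0.05 is actually written and which are primary on both lists. If independent, it is 34% in either direction and 18% in favour of the template. The 10- and 11-test figures also assume 0.05 for the χ² tests and, for the eleventh, some test of complications.

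All figures assume that each angle is tested separately and that no effect is real. The correlations are assumptions. Only near-complete correlation brings the directional rate close to nominal (6.0% to 6.6% at 0.9, against 2.5%), and nothing in the article suggests correlation that high across such different measures.

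**What to change.** 1. Reconcile the Abstract with the Primary outcomes section so that there is one list.
2. Name one primary outcome, tested at two-sided 0.05: the proportion on which the sample size was calculated. The article does not name that proportion. Screw position per patient on the day 1 CT is the likely candidate, but the safety wording could also fit complications, so the sponsor must confirm it.
3. Make the other outcomes, including X-ray exposure, secondary. Either apply Holm's correction across them or report them as estimates with 95% confidence intervals.

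The cost is wording in the Abstract, Outcome measure and Statistical analysis sections, and a registry update. No patients or data are added, and the 132-per-arm calculation stands if the named outcome is the one that was sized. The downside is that the demoted outcomes face stricter thresholds or carry no confirmatory claim.

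If the sponsor keeps several primaries with Holm's correction, the protocol should say that any one of them may support a claim and should restate the power. That route is not free: on the plan's own proportions, power at the first-step level for 11 tests is about 48% at 132 per arm.

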**Methods and analysis:**

Patients who meet the criteria of the surgery will be randomly divided into experimental groups and control groups by a computer-generated randomisation schedule. We will preoperatively design an individual 3D navigation template using CATIA software and MeditoolCreate. The following primary outcomes will be collected: screw angles compared with the optimal screw trajectories in 3D digital images, length of the wound incision, operative time, intraoperative blood loss and complications. The following secondary outcomes will be collected: visual analogue scale (VAS) for back pain, VAS for leg pain and the Oswestry Disability Index. These parameters will be evaluated on day 1 and then 3, 6, 12 and 24 months postoperatively.

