**Trial registration number:**

ChiCTR-IDR-17010466

Strengths and limitations of this studyThis is the first multicentre randomised controlled trial to compare a three-dimensional (3D) navigation template for guiding a unilateral lumbar pedicle screw with contralateral translaminar facet screw fixation versus traditional multiple X-ray fluoroscopy.We will first use Mimics and CATIA software to design the 3D navigation template of a unilateral lumbar pedicle screw with contralateral translaminar facet screw fixation.The clinical data will be collected prospectively at least 24 months after the operation.Because this is a multicentre randomised controlled trial, the surgeons’ experiments at different research sites may influence the outcomes.

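### The VAS and ODI analysis stops at 12 months although 24-month scores are collected, and it uses the preoperative score as a repeated outcome rather than as a covariate

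*Protocol article*

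**What the plan says.** The secondary outcomes are back-pain VAS, leg-pain VAS and ODI. On their timing, the protocol article's Secondary outcomes section states: "The data will be collected preoperatively; on day 1 postoperatively; and then at 3, 6, 12 and 24 months postoperatively". Table 1 marks all three at the same six visits. The abstract agrees on follow-up: "These parameters will be evaluated on day 1 and then 3, 6, 12 and 24 months postoperatively". The strengths and limitations list after the abstract offers the length of follow-up as a feature of the study: "The clinical data will be collected prospectively at least 24 months after the operation".

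The Statistical analysis section is narrower. Its list of VAS and ODI time points opens with the preoperative, postoperative and 3-month scores and closes: "6 months postoperatively and 12 months postoperatively will be analysed using a repeated-measures analysis of variance". It mentions no 24-month score and no baseline covariate, and it does not say which term (group, or group by time) is the test. No other section assigns the 24-month scores an analysis or explains why they are left out. The Discussion says VAS and ODI will be compared and sets no 12-month limit.

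**The concern.** There are two separate issues in one sentence.

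**The 24-month visit.** The list of analysed time points is explicit, so it conflicts with the collection schedule; it is not silent on a detail that an analysis plan could fill in. An analyst who follows it makes no between-arm comparison at the last visit for any patient-reported outcome. If 24 months is added later, that decision is taken once data exist, which leaves room for selective reporting.

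**The preoperative score.** It is one level of the repeated factor. Randomisation makes the arms equal in expectation at that level, so a group effect averaged over all levels includes one where no effect can exist. The score is also not used to explain between-patient variation in later scores. The cost is precision; type I error is not affected.

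**Working it through.** **Step 1: visits collected and analysed** (taking postoperation in the analysis sentence to mean day 1)

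| Time point | Collected (abstract, Table 1, Secondary outcomes) | Analysed (Statistical analysis) |
|---|---|---|
| Preoperative | yes (Table 1, Secondary outcomes) | yes, as an outcome level |
| Day 1 | yes | yes |
| 3 months | yes | yes |
| 6 months | yes | yes |
| 12 months | yes | yes |
| 24 months | yes | no |

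Six visits are collected and five analysed. One of the five postoperative visits (20%), the last, is left out for all three outcomes.

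**Step 2: what 132 means.** The Sample size calculation section uses 84.6% and 95%, "with a power (1−b) of 0.8 and α of 0.05", and reports 132 without saying whether this is per arm or in total. With a two-sided test, pooled variance and no continuity correction, and mean proportion 0.898:

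n per arm = [1.96·√(2·0.898·0.102) + 0.8416·√(0.846·0.154 + 0.95·0.05)]² / 0.104² = (0.8389 + 0.3549)² / 0.010816 = 131.8, so 132.

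The figure therefore reproduces per arm (264 in total). None of the usual variants (one-sided, continuity-corrected, unpooled, arcsine) gives 132 as a total. Because the label is missing, both readings are carried below. The calculation rests on a proportion and does not size the VAS or ODI comparisons.

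**Step 3: dilution of the group main effect.** With no expected difference at baseline and a constant difference d at four postoperative visits, the group effect averaged over five levels is (0 + 4d)/5 = 0.8d.

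**Step 4: power.** Assumptions, none of them in the documents: d = 0.4 SD, equal correlation ρ = 0.5 between all visits, two-sided α of 0.05, normal approximation. Variances are in units of σ².

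- Five-level mean: (1 + 4ρ)/5 = 0.60; effect 0.8 × 0.4 = 0.32.
- Mean of four postoperative visits adjusted for baseline: (1 + 3ρ)/4 − ρ² = 0.625 − 0.25 = 0.375; effect 0.40.
- z = effect / √(2·variance/n); power = Φ(z − 1.96).

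| n per arm | Planned main effect | Baseline-adjusted |
|---|---|---|
| 66 (132 is the total) | z = 0.32/√(1.20/66) = 2.37, power 66% | z = 0.40/√(0.75/66) = 3.75, power 96% |
| 132 (132 is per arm) | z = 0.32/√(1.20/132) = 3.36, power 92% | z = 0.40/√(0.75/132) = 5.31, power over 99% |

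The ratio of sample sizes for equal power does not depend on n: (0.60/0.8²)/0.375 = 0.9375/0.375 = 2.5.

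**Step 5: sensitivity to the correlation.** At ρ = 0.4 and 0.6 the same formulas give 72% and 61% against 96% and 98% with 66 per arm, and 95% and 88% against over 99% with 132 per arm. If baseline correlates only 0.2 with later scores while later scores correlate 0.5 with each other, the variances become (5 + 2·(4·0.2 + 6·0.5))/25 = 0.504 and 0.625 − 0.04 = 0.585. Power is then 74% against 85% with 66 per arm and 96% against 99% with 132.

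**Step 6: if another term is tested.** Set the baseline-adjusted analysis of the same four visits to 80% power at ρ = 0.5, so z = 2.80.

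- Mean change from baseline: variance 0.625 + 1 − 2·0.5 = 0.625, z = 2.80·√(0.375/0.625) = 2.17, power 58%.
- Group-by-time test on 4 df: noncentrality 1.6·d² with d² = 2.80²·0.375 = 2.94, giving 4.71 and power 37%.
- Five-level main effect, for comparison: 42.5%.

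For ρ from 0.3 to 0.7 these three run 46–69%, 28–47% and 55–28%. All stay below 80%.

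**The case against.** The 24-month mismatch has no good defence. The baseline part does attract fair objections.

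- *The method is valid.* This stands. A repeated-measures ANOVA with baseline as a level does not bias the comparison under randomisation. The gain from adjustment is in efficiency, and covariates and contrasts are often left to an analysis plan. The baseline change is therefore an improvement to make in the same edit, not the correction of an error.
- *The power gap depends on assumptions.* This stands too. With 132 per arm, the only reading that the protocol's own inputs reproduce, the planned main effect keeps at least 88% power for ρ between 0.4 and 0.6. Equal correlation across surgery flatters the adjusted analysis, and a constant effect from day 1 to 12 months is also assumed.
- *The tested term is not named.* The 4/5 dilution applies to the group main effect only; it does not describe a group-by-time test or visit-wise comparisons. Step 6 shows that the other terms also lose efficiency, but by a different route.

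Two stronger readings should be resisted. A reader might infer that every patient with a missing visit drops out of the analysis, as standard software would do. The Monitoring section instead has the data of patients lost to follow-up replaced by the average. Whether that is sound is a separate question, but it is not deletion. A reader might also infer that the trial discards its main endpoint. VAS and ODI are listed as secondary; what is missing is the analysis of their last time point.

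**Conclusion.** The contradiction is established from the text alone: three places schedule the 24-month VAS and ODI scores, and the analysis sentence omits them. One of five postoperative visits would go uncompared for all three secondary outcomes.

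The baseline handling is inefficient but unbiased. The 4/5 dilution is exact for a group main effect under a constant postoperative difference. The power figures are illustrations that rest on an assumed correlation, an assumed effect of 0.4 SD and an unresolved label on 132: the shortfall is about 30 percentage points if 132 is the total, about 8 if it is per arm, and smaller with a weaker baseline correlation.

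Severity is moderate. The outcomes are secondary and the sample size was not based on them.

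**What to change.** - Add 24 months to the VAS and ODI time points in the Statistical analysis section, so that the analysis matches Table 1.
- Analyse the day 1, 3, 6, 12 and 24-month scores in a longitudinal model (for example a mixed model for repeated measures) with arm, visit, arm by visit and the preoperative score as covariate.
- Report the adjusted between-arm difference with 95% CI at each visit, including 24 months, and state which visit or contrast is of main interest.

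A longitudinal model that keeps baseline in the response but constrains the arm means to be equal there would recover the same efficiency. The cost is wording only: every score needed is already scheduled. The change should be made and dated before outcome data are examined.
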